### Randomization and blinding process

An assistant researcher specially trained will be responsible only for recruiting the participants to enter the study and will give them all the information about the study, obtaining their written consent in case they agree to participate.

An assistant researcher not involved with the recruitment, intervention and assessment will generate the allocation sequence. The participants will be allocated in a group that will receive a low-calorie diet for weight loss (group I) or in another group that will receive diet + PFMT (group II). Randomization will be carried out using a computational list of random numbers and will be concealed (by means of a sealed brown envelope). Women’s data will be kept only with the assistant researcher not involved with other parts of the research process to process to protect confidentiality before, during, and after the intervention. The trial is an assessor blinded in relation to the pelvic floor muscle assessment.

The senior researcher who is not involved with the recruitment, intervention delivery, and assessment will have access to the trial data. We have planned to submit the manuscript to an open-access journal that makes all data available to readers as an appendix or under request.

Figure 1 shows the flowchart for selecting women for the randomized clinical trial, following the CONSORT.

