The sets will be performed only in two positions at the face-to-face supervised sessions at the hospital: sitting and standing (2 sitting sets + 2 standing sets). The participants of this group will be instructed to perform PFMT at home at least three times a week, except on the days of supervised training. They will be instructed to follow the booklet given to them in the first meeting, in addition to the fortnightly adherence diary to the exercises to be filled weekly. Participants will also be instructed on how to perform the “the knack” maneuver, which consists of repeatedly contracting their PFM before any increase in intra-abdominal pressure during daily activities [14]. Women will also be instructed to repeatedly contract their PFM when they feel urgency. Women will fill a diary about their adherence to PFMT, and there will be a place where they are asked about any side effects or bother related to the intervention. At the last assessment, they are asked about again about any unintended effects related to the trial intervention. The type and number of unintended effects will be fully reported as an important result of the trial. Although adverse effects of these type of intervention is not very common or severe, all the participant is assured they can discontinue their participation at any time for any reason, including any adverse effects (Table 1). Table 1 presents detailed information about the protocol of intervention.

**Table 1 Tab1:** Stages of the study and information about the 12 weeks training

	Recruitment	
	1^st^ Physical therapy evaluation	
	Randomization	
Week 1	Face-to-face session	4 sets (2 sitting sets + 2 standing sets) of ten maximum perceived voluntary contractions sustained for 6 s with a 6-s resting period between the contractions. At the end of a series of 10 contractions, five rapid contractions of the PFM will be performed. Two minutes interval will be given between each set performed in each position
Week 2	Face-to-face session	4 sets (2 sitting sets + 2 standing sets) of ten maximum perceived voluntary contractions sustained for 6 s with a 6-s resting period between the contractions. At the end of a series of 10 contractions, five rapid contractions of the PFM will be performed. Two minutes interval will be given between each set performed in each position

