Week 9	Face-to-face session	4 sets (2 sitting sets + 2 standing sets) of ten maximum perceived voluntary contractions sustained for 6 s with a 6-s resting period between the contractions. At the end of a series of 10 contractions, five rapid contractions of the PFM will be performed. Two minutes interval will be given between each set performed in each position
Week 10	Face-to-face session	4 sets (2 sitting sets + 2 standing sets) of ten maximum perceived voluntary contractions sustained for 6 s with a 6-s resting period between the contractions. At the end of a series of 10 contractions, five rapid contractions of the PFM will be performed. Two minutes interval will be given between each set performed in each position
Week 11	Face-to-face session	4 sets (2 sitting sets + 2 standing sets) of ten maximum perceived voluntary contractions sustained for 6 s with a 6-s resting period between the contractions. At the end of a series of 10 contractions, five rapid contractions of the PFM will be performed. Two minutes interval will be given between each set performed in each position
Week 12	Face-to-face session	4 sets (2 sitting sets + 2 standing sets) of ten maximum perceived voluntary contractions sustained for 6 s with a 6-s resting period between the contractions. At the end of a series of 10 contractions, five rapid contractions of the PFM will be performed. Two minutes interval will be given between each set performed in each position
	2^st^ Physical therapy evaluation (Group I and II)	
	Diary about the adherence to PFMT	Women will fill a diary about their adherence to PFMT, and there will be a place where they are asked about any side effects or bother related to the intervention. At the last assessment, they are asked about again about any unintended effects related to the trial intervention. The type and number of unintended effects will be fully reported as an important result of the trial. Although adverse effects of these type of intervention are not very common or severe, all the participant is assured they can discontinue their participation at any time for any reason, including any adverse effects

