#### Other outcome measures

The adherence to home PFMT sessions will be monitored by the physiotherapist from a diary where women will register their adherence to home training. This diary will be attached to the leaflet that will be given to women in the first session. The diary will be collected by the physiotherapist every fortnight.

The PFM function will be assessed using vaginal palpation by a trained physiotherapist who will not be involved with the intervention and will not be aware of women’s allocation in the groups. Before the start of the palpation exam, the woman will receive detailed information about the anatomy, function, and dysfunction of the PFM and how to contract them correctly. The evaluation will be carried out with the participant in the supine position with the hip and knee semi-flexed. The participant will be asked to pull their PFM in and up as hard as possible, and then she will be instructed to relax them completely. Contraction of PFM will be classified as absent or present. The ability to contract the PFM will be considered present when there is occlusion and/or occlusion and elevation of the PFM towards the pubic symphysis and absent when there is no perceived internal movement. Additionally, muscle contraction will be graded according to the Modified Oxford Grading Scale (MOGS) [15, 16]. Contractions of muscles such as gluteus, adductor, and abdominal will be discouraged by the examiner.

Self-perception of women’s PFM contraction will be assessed at the time of the physical evaluation when the examiner will ask the participant if she feels she is able to contract her PFM and she will be asked to estimate the intensity of her PFM according to the MOGS that will be presented to her [17].

Participants’ subjective satisfaction with the treatment will be measured by the visual analog scale (VAS), which is an estimate on a numerical scale where 0 represents no satisfaction at all and 10 means the maximum possible satisfaction with the treatment.

In relation to satisfaction with the interventions, participants will be asked to answer the following questions: “Are you satisfied with the treatment you received for UI?”, “Would you do this treatment again?”, “Would you recommend this treatment?”, “Would you pursue another treatment?”. The options of answers to these questions are yes or no.

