### Data collection

The data will be collected in an interview format using a self-reported validated questionnaire and PFM exam. A trained assistant researcher will conduct an interview and a PFM assessment. All assessments will be performed (at baseline) and after 12 weeks for both groups and will be performed by the same researcher that will be blind about women’s group allocation.

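### Both described harms prompts ask only about effects linked to the intervention, so the promised count of unintended effects will probably be too low and will depend on participants' expectations

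*Protocol article*

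**What the plan says.** The Intervention section of the protocol article describes two points at which harms are elicited.

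- **PFMT diary:** a space in the diary asks women about "any side effects or bother related to the intervention".
- **Last assessment:** "they are asked about again about any unintended effects related to the trial intervention".

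The diary row of Table 1 repeats both. The reporting commitment follows: "The type and number of unintended effects will be fully reported as an important result of the trial".

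Three other statements bear on how these prompts work.

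- **Blinding:** "The trial is an assessor blinded in relation to the pelvic floor muscle assessment". Participant blinding is not claimed, and diet alone cannot be disguised as diet plus supervised exercise.
- **Who assesses:** under Data collection, the assessments of both groups at baseline and 12 weeks "will be performed by the same researcher that will be blind about women’s group allocation".
- **Who holds the diary:** under Other outcome measures, "This diary will be attached to the leaflet that will be given to women in the first session". The diary records home exercise, so in effect only group II has it.

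**The concern.** Whether a symptom is an unintended effect of treatment is something a randomised comparison can help to answer, provided events are recorded whatever their supposed cause and then compared between arms. Here the question of cause comes first and the participant answers it. An event she puts down to her weight, her age or chance does not fit the prompt. If it is not recorded, nobody can reclassify it later.

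Two consequences follow. The count will tend to be too low. It will also depend on belief: women doing pelvic floor exercises have more reason to connect a pelvic symptom with their treatment than women on diet alone, so the two arms may filter differently. Blinding the assessor does not help, because the filter is applied by the woman and not by the person asking.

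The trial intends to present this count as an important result, so the way it is obtained matters. The primary continence outcomes are not affected.

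**Working it through.** The plan states no harms rate, so there is no figure to reproduce. The main check is of the text.

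**1. Is the filter in both prompts?** Yes. The diary item and the last-assessment item are each limited to effects connected with the intervention. Table 1 repeats the wording without widening it.

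**2. Who applies it?** The woman. She completes the diary and answers the question at the last assessment, and she knows which treatment she has had.

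**3. Does the article describe a route without the filter?** Not for adverse events in general.
- The physiotherapist meets or telephones group II every week. The calls are described as encouragement to exercise, and no recording of harms is mentioned.
- Women may leave the trial because of any adverse effect, but recording of the reason is not described.
- The ICIQ-SF and the muscle examination are unfiltered, but cover only continence and muscle function.

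**4. Is there a known risk that the prompts would miss?** The Ethic section lists discomfort during vaginal palpation. That arises from an assessment procedure, so a literal reading of either prompt leaves it out.

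**5. Direction of the effect.** Let *r* be the true event probability, *n* the number of women in an arm and *a* the share of events that a woman attributes to the intervention. The expected number recorded is *n* × *r* × *a*. Any *a* below 1 lowers it. If the arms have the same *n* and *r* but different shares, the ratio of recorded counts is *a*(II)/*a*(I), whatever *n* and *r* are. A difference between arms can then arise from attribution alone.

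**6. Illustration, on assumptions only.** Take *r* = 0.20 and *n* = 11. The 11 assumes that the 22 participants in Sample size calculation are the total, split equally; the article gives no figure per arm. The chance of recording no event in an arm is (1 − 0.20 × *a*)^11.

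| Share attributed (assumed) | Calculation | Chance of recording none | Expected number recorded |
|---|---|---|---|
| 1 | 0.80^11 | 0.086 | 11 × 0.20 × 1 = 2.2 |
| 0.5 | 0.90^11 | 0.314 | 11 × 0.20 × 0.5 = 1.1 |
| 0.25 | 0.95^11 | 0.569 | 11 × 0.20 × 0.25 = 0.55 |

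The rate and the shares are not taken from the documents. The table shows how the mechanism works and is not evidence of how large the problem is.

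**The case against.** The strongest reply is that the article summarises the diary and the interview and shows neither form. The real items may be neutral, and adverse-event forms and relatedness procedures commonly sit in a full protocol that is not shown. This stands as a limit on certainty. It does not remove the point, which rests on how the article states its prompts and not on what it leaves out. If the forms are already neutral, correcting the article's description settles the matter.

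Other objections stand and limit what can be claimed.

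- **A reader might infer that every event a woman does not attribute is lost.** The documents do not support that. Worsening incontinence is measured by the ICIQ-SF in both arms at baseline and 12 weeks, and muscle function is re-examined. Women are asked about barriers to adherence, and concomitant pelvic floor treatment is to be monitored. These do not replace general adverse-event collection, but they carry no such filter.
- **A reader might infer that effects blamed on the diet are excluded.** They are not. The last-assessment prompt refers to the trial intervention, and the diet is part of it.
- **A reader might infer that the plan contradicts its own promise.** It does not. The promise concerns unintended effects, not all adverse events. The weakness is that these prompts are an unreliable way of counting even those.
- **A reader might infer that the trial sets out to show that harms are rare.** The remark that adverse effects are neither common nor severe is background about this type of treatment.

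Finally, neutral wording placed only in the PFMT diary would make matters worse. It would collect background symptoms repeatedly in group II and at most once in group I. That is correct, and the fix has to allow for it.

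**Conclusion.** The point holds in a limited form. As the article describes them, both harms prompts make unmasked participants judge cause before anything is recorded, and events they do not attribute to the trial intervention are not asked for. The reported type and number of unintended effects will therefore probably be understated and will depend on expectations.

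This rests on two assumptions: that the forms follow the article's wording, and that women attribute fewer than all of their events. The direction follows from those alone. The size is unknown, since the documents contain no event rate, attribution share or per-arm number. The change is worth making before recruitment, but this is a weakness in how harms are collected and does not affect the efficacy comparison.

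**What to change.** Replace the two prompts in the Intervention section and Table 1 with one cause-neutral question, for example: *Since we last spoke, have you had any new symptom or health problem, or has any existing one become worse, whatever you think the cause?*

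- **Same question and same schedule in both groups.** At minimum, ask it at the 12-week assessment. Put any interim prompt to both arms at contacts they already share, such as the monthly nutrition meetings, using a fixed script. Do not place the neutral question only in the PFMT diary.
- **Judge relatedness afterwards.** Use someone not told the allocation, with references to exercise sessions removed from the event descriptions where possible. The senior researcher named under Randomization and blinding process has access to the trial data and is not said to be blinded, so independence from delivery and assessment is not enough.
- **Report** all events by arm, then the subset judged related.

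The cost is rewording two prompts, adding a question at existing contacts and some extra coding, with no new visit. The downside is that more events will be listed, many of them unrelated, so the count will look less favourable. Trials status says that recruitment has not begun, so the change can be made before any data are collected.

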### Assessment

#### Primary outcome measures

Self-report of urinary incontinence will be measured by question 3 of the ICIQ-SF. Women will be considered incontinent if they choose options 1, 2, 3, 4, or 5 of question 3. Women will be considered continent if they choose option 0 in question 3.

The severity and impact of urinary incontinence on women’s quality of life will be measured by the ICIQ-SF score.

#### Other outcome measures

The adherence to home PFMT sessions will be monitored by the physiotherapist from a diary where women will register their adherence to home training. This diary will be attached to the leaflet that will be given to women in the first session. The diary will be collected by the physiotherapist every fortnight.

The PFM function will be assessed using vaginal palpation by a trained physiotherapist who will not be involved with the intervention and will not be aware of women’s allocation in the groups. Before the start of the palpation exam, the woman will receive detailed information about the anatomy, function, and dysfunction of the PFM and how to contract them correctly. The evaluation will be carried out with the participant in the supine position with the hip and knee semi-flexed. The participant will be asked to pull their PFM in and up as hard as possible, and then she will be instructed to relax them completely. Contraction of PFM will be classified as absent or present. The ability to contract the PFM will be considered present when there is occlusion and/or occlusion and elevation of the PFM towards the pubic symphysis and absent when there is no perceived internal movement. Additionally, muscle contraction will be graded according to the Modified Oxford Grading Scale (MOGS) [15, 16]. Contractions of muscles such as gluteus, adductor, and abdominal will be discouraged by the examiner.

Self-perception of women’s PFM contraction will be assessed at the time of the physical evaluation when the examiner will ask the participant if she feels she is able to contract her PFM and she will be asked to estimate the intensity of her PFM according to the MOGS that will be presented to her [17].

Participants’ subjective satisfaction with the treatment will be measured by the visual analog scale (VAS), which is an estimate on a numerical scale where 0 represents no satisfaction at all and 10 means the maximum possible satisfaction with the treatment.

In relation to satisfaction with the interventions, participants will be asked to answer the following questions: “Are you satisfied with the treatment you received for UI?”, “Would you do this treatment again?”, “Would you recommend this treatment?”, “Would you pursue another treatment?”. The options of answers to these questions are yes or no.

In order to identify barriers to treatment, the participants will be asked to answer the following questions: “Do you identify any barriers or difficulties in adhering to the treatment you received for urinary incontinence? If any please list the barriers.”

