**Methods:**

This is a protocol for a randomized controlled trial that will include obese women reporting UI and being able to contract their pelvic floor muscles. The participants will be randomly allocated in two groups: group 1 will participate in a 12-week protocol of low-calorie diet delivered by a multi-professional team at a tertiary hospital; group II will receive the same low-calorie diet protocol during 12 weeks and will additionally participate in 6 group sessions of supervised PFMT delivered by a physiotherapist. The primary outcome of the study is self-reported UI, and severity and impact of UI on women’s quality of life will be assessed by the ICIQ-SF score. The secondary outcomes will be adherence to the protocols assessed using a home diary, pelvic floor muscle function assessed by bidigital vaginal palpation and the modified Oxford grading scale, and women’s self-perception of their PFM contraction using a questionnaire. Satisfaction with treatments will be assessed using a visual analog scale. The statistical analysis will be performed by intention to treat and multivariate analysis of mixed effects will be used to compare outcomes. The complier average causal effects (CACE) method will be used to assess adherence. There is an urgent need for a high-quality RCT to investigate if the association of a low-calorie diet and PFMT can provide a larger effect in the improvement of urinary incontinence reports in women with obesity.

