### Inclusion criteria

Women over 18 years, with a body mass index (BMI) > 30 kg/m^2^; reporting stress urinary incontinence, urgent urinary incontinence, or mixed urinary incontinence in the past 4 weeks assessed by the ICIQ-SF; who are able to contract the pelvic floor muscles (assessed using vaginal palpation with a PFM contraction ≥ 2 according to the modified Oxford grading scale); and without any cognitive impairment.

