### Statistical analysis

Data will be de-identified, encoded, and stored in the database using the Excel Program. The software SPSS 22.0 will be used for the analysis of data. The description of quantitative variables will be expressed in mean, standard deviation, minimum value, median and maximum value. Qualitative variables will be described in absolute and relative values (%). A 95% confidence interval and 0.05 significance will be considered for all tests. Both per-protocol and intention-to-treat analyses will be performed.

A linear mixed-effect model will be used to analyze the ICIQ-SF score. In the reassessment, individuals’ values will be considered random effects, and the groups, the times, and the interaction between them will be regarded as fixed effects. In addition, the McNemar test will verify changes in categories variables before and after the intervention. Both per-protocol analysis [11–13] and an intention-to-treat analysis will be also conducted.

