## Discussion

We presented a protocol of a RCT that will investigate the efficacy of a 12-week pelvic floor muscle training (PFMT) program added to a low-calorie diet on obese women with urinary incontinence (UI) reports. In the literature, the benefits of weight loss to improve UI is established by the literature [6] but it is yet to be evidenced if PFMT could increase the effectiveness of weight loss on UI reports in obese women.

Weight loss, both mediated by surgical and conservative interventions, is effective to improve all types of non-neurological UI (stress, urgency, or mixed) [18, 19]. In fact, a loss of 5 to 10% of weight provides a significant improvement in UI complaints, and weight loss is considered a first-line therapy.

High obesity rates are a current global reality and reports of UI by this population have a high prevalence. When compared to a normal body mass index, overweight was associated with a one-third increase in the risk of UI (relative risk = 1.35, 95% confidence interval = 1.20–1.53), while the risk was doubled in obese women (relative risk = 1.95, 95% confidence interval = 1.58–2.42).

On the other hand, weight loss will not provide an active improvement of PFM function as PFMT, the gold standard physiotherapy intervention to treat non-neurogenic UI in women. The updated Cochrane review on this topic included randomized and quasi-randomized controlled trials investigating the effect of PFMT on UI in women. The search produced 1299 records, from which 94 potentially relevant full-text articles were retrieved. The inclusion of new studies in this updated review reinforced the results showing the effectiveness of PFMT in the treatment of any type of non-neurogenic UI in women [20].

In planning our RCT protocol, we considered what is already known from the literature to optimize the PFMT effectiveness having in mind that is essential to provide a high-quality intervention based on exercise physiology. We will include only women who are able to contract their PFM, providing education to them related to PFM function, dysfunction, and how to contract correctly their PFM as part of our intensive and supervised PFMT protocol.

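### The absent/present contraction rating cannot show gain because eligibility fixes it at baseline, and the only test named for categorical variables neither compares the arms nor suits the Oxford grade

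*Protocol article*

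**What the plan says.** Eligibility: the Inclusion criteria of the protocol article require ability to contract, "assessed using vaginal palpation with a PFM contraction ≥ 2 according to the modified Oxford grading scale". The Discussion repeats it: "We will include only women who are able to contract their PFM".

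Outcome: Study design makes PFM function a secondary outcome. Other outcome measures describes the palpation and says "Contraction of PFM will be classified as absent or present". The two categories are defined there: "The ability to contract the PFM will be considered present when there is occlusion and/or occlusion and elevation of the PFM", and "absent when there is no perceived internal movement". The same paragraph adds a grade on the Modified Oxford scale. The abstract and Table 2 describe PFM function as palpation with Oxford grading. Table 2 schedules it at baseline and post-intervention and has no separate row for absent/present.

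Analysis: the Statistical analysis section gives a linear mixed model for the ICIQ-SF score and then states that "the McNemar test will verify changes in categories variables before and after the intervention". It assigns no method to the Oxford grade by name. The abstract is broader: "multivariate analysis of mixed effects will be used to compare outcomes".

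**The concern.** There are two linked problems. First, a rating that sits in the outcome description has its baseline value fixed by the entry rule. If it is reported as a result, it will be at or near 100% present at both visits in both arms, whatever happened to muscle strength.

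Second, the one test stated for categorical variables is a paired before/after test. Study design calls this a superiority trial of diet plus PFMT against diet alone, so the question is whether change differs between arms. A within-arm test does not answer it. Standard McNemar also needs two categories, while the Oxford grade has several ordered ones and no cut point is given.

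At stake is the trial's view of its own mechanism. The Discussion argues that PFMT actively improves PFM function and weight loss does not. That contrast between arms deserves a named endpoint and a method that tests it.

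**Working it through.** **Step 1. Baseline value of the binary rating.** Entry needs a palpated contraction of grade 2 or more. Table 1 places the first physical therapy evaluation before randomisation. The article does not define the Oxford grades, so the mapping rests on its own words: eligible women are able to contract, and ability to contract is what present means. Hence 100% are present at baseline, and the absent-to-present cell is 0 in each arm.

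**Step 2. What McNemar can then show.** Inputs: 22 participants (Sample size calculation). The allocation ratio is not stated; I assume 11 per arm. With one discordant cell fixed at 0 and k women moving from present to absent, the exact two-sided p-value is min(1, 2 × 0.5^k).

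| k losses among 11 | exact p |
|---|---|
| 0 | 1.00 (no discordant pairs) |
| 4 | 2 × 0.5^4 = 0.125 |
| 5 | 2 × 0.5^5 = 0.0625 |
| 6 | 2 × 0.5^6 = 0.031 |

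The test can reach 0.05 only through six or more losses. It has no route to showing gain.

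**Step 3. The Oxford grade on the same women.** Suppose all 11 in one arm rise one grade. The binary rating has no discordant pairs, so p = 1.00. An exact sign test on the grades gives 2 × 0.5^11 = 0.001. The grade therefore carries the information that the binary rating loses. This is still a within-arm test and serves only to compare the two scales.

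**Step 4. A between-arm analysis of the grade (illustration only).** The documents give no grade distribution or expected shift, so all of these are assumed: 11 per arm; baseline grades 2/3/4 in 40/40/20%; 15% of group I rise one grade; 10% of those who do not rise fall one grade. Rank ANCOVA of the 12-week grade on arm and baseline grade, 4,000 simulated trials per setting:

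| Group II rising one grade | rejection rate |
|---|---|
| 15% (no difference) | about 4% |
| 60% | about 52% |
| 70% | about 70% |
| 80% | about 86% |

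These show that a baseline-adjusted comparison is workable at this size if shifts are large. They are not a forecast, and the point does not depend on them.

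**Step 5. The two analysis statements side by side.** The Statistical analysis section names the mixed model for the ICIQ-SF score and McNemar for categorical variables. The abstract applies mixed effects to outcomes without restriction. A reader cannot tell which of the two governs the Oxford grade.

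**The case against.** The strongest reply is that absent/present was never an endpoint. The abstract and Table 2 name the Oxford grade, and the binary call may be a step of the examination that also serves screening. That reading is possible, but the text places the rating under outcome measures, introduces the grade as an addition to it, and nowhere limits it to eligibility. One sentence would settle it.

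A reader might go further and infer that PFM function as a whole cannot improve, or that the analysis section can yield only the result that cannot improve. The documents do not support this. The grade is recorded at both visits, entry at grade 2 leaves higher grades open, descriptive summaries are planned for all variables, and the abstract leaves room for a mixed model.

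It can also be said that McNemar extends to several categories through Bowker's symmetry test, and that the article contains a yes/no item McNemar does fit (whether the woman feels able to contract). Both are true. Bowker's test, however, ignores the order of the grades and is still within one arm. Take 11 women all rising one grade, split 4, 4 and 3 over three adjacent pairs: the statistic is 4 + 4 + 3 = 11. On 3 df (non-empty pairs) p = 0.012. On 6 df (assuming grades 2 to 5, 4 × 3/2 = 6 pairs) p = 0.088. The sign test gives 0.001.

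Finally, the model for a secondary ordinal scale is often left to an analysis plan, which is not shown. Its absence alone would be no finding. What remains is a stated test that does not compare the arms, and two statements of different scope.

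**Conclusion.** The point holds in limited form. The absent/present rating is uninformative as an outcome, since all women are present at baseline and only loss can be recorded. The Oxford grade is not affected and can show improvement. The only test stated for categorical variables is within-group and, in its standard form, for two categories, so it neither compares the arms nor suits the grade. The abstract and the Statistical analysis section should say the same thing about which outcomes the mixed model covers.

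This is minor. It concerns one secondary outcome and changes neither the data collected, the primary outcome nor the sample size. It rests on the article's equating of eligibility with ability to contract and, for the p-values, on equal allocation of the 22 participants.

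**What to change.** - In Other outcome measures, state that absent/present is used only to confirm eligibility, and name the Oxford grade at 12 weeks as the PFM-function endpoint.
- In Statistical analysis, replace McNemar for this endpoint with a between-group comparison of the 12-week grade adjusted for baseline grade, by a proportional-odds model or rank ANCOVA. With about 11 per arm and sparse grades, rank ANCOVA is the safer choice if the proportional-odds fit is unstable.
- Word the abstract and the Statistical analysis section alike on which outcomes the mixed model covers.

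The cost is a few sentences. Palpation and grading are already scheduled at both visits, so no measurement is added, and Trials status says recruitment had not begun. The small downside is that an ordinal result is slightly harder to present than a percentage; a table of grades by arm and visit would deal with most of that.
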